### Aims and objectives

The goal of our study is to determine whether allowing participants to choose from a selection of appropriate diet and exercise plans, within the context of a randomised controlled trial evaluating four different support strategies, enhances adherence and promotes greater weight loss and positive health outcomes. Giving people the choice of which diet and exercise regime is best incorporated into their particular lifestyle is expected to improve adherence, reflects real-world conditions, and is consistent with the lack of evidence for meaningful differences between diet modalities. Acknowledging this concept in conjunction with testing different support strategies offers a unique opportunity to determine how best to support individuals to make dietary and exercise changes under real-world conditions.

The primary aim of our study is to determine the effectiveness of different support strategies (control condition, brief support, daily self-weighing, app use, hunger training) on weight loss at 12 and 24 months. Secondary aims are to determine:(i)the effect of different support strategies on body composition, dietary intake, exercise, inflammatory markers, blood lipids and lipoproteins, adiponectin, ghrelin, and psychosocial indices at 12 and 24 months(ii)the degree of adherence to each of the support strategies over the 24 months(iii)the degree of adherence to each of the diet (Mediterranean, intermittent fasting, modified Paleo) and exercise (current recommendations, HIIT) plans that are selected over the 24 months and the outcomes within these self-selected groups.

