## Methods/Design

### Study design

The Support strategies for Whole food diets, Intermittent Fasting and Training (SWIFT) study is a 5-arm randomised controlled trial testing the effectiveness of different support strategies for encouraging appropriate behaviour change for effective weight management. Participants will be randomised to one of the five groups for a 12-month intervention, with further follow-up at 24 months (Fig. 1) to determine whether any changes have been sustained. The primary analysis will be modified intention to treat (using all available data) and will focus on the outcomes resulting from the different support strategies (RCT analysis).

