### Intervention groups and sessions

*Control* – those randomised to the control condition will meet with research staff to discuss which diet and exercise options would suit them best. They will also receive the resource detailing the evidence-based behavioural weight loss strategies noted above. They will then be left to their own devices for the remainder of the study (except for attending all outcome assessments).*Regular brief support* – Participants in this group will attend an appointment at the study clinic once a month to be weighed. During this time they will have the opportunity for a 5–10 minute conversation with research staff to assess progress, review and brainstorm solutions to problems if any exist, and encourage adherence. These sessions are modelled on our successful *HEAT* study and provide an opportunity for support and ongoing assistance with strategies [22].*App* – Participants in the app group will attend an appointment to learn how to use MyFitnessPal to monitor their energy and macronutrient intakes. They will be provided with assistance in setting up their MyFitnessPal account to be compatible with their chosen diet, and will be shown how to use the app on their smartphone and/or computer. Participants will be asked to monitor their dietary intake every day for the first month, and for one week of every month for months 2–12.*Daily self-weighing* – Individuals randomised to this group will receive instruction and support about weighing themselves every day (same time of day and degree of clothing). Participants will text their weight or enter it online using a web page connected to our secure database each day which will have a graphical display. Progress and adherence to entering/sending weight data will be checked every week and reminder texts sent where necessary. Every month, research staff will provide personalised progress feedback and support by email.*Biochemical hunger training* – This group will follow a 4-week protocol that trains them to recognise “real” (biochemical) hunger by associating feelings of hunger with blood glucose levels following fingerprick testing with portable glucometers. Our protocol is based on that of Ciampolini et al. [45] but adapted slightly following piloting. In the original method, participants are only able to eat if blood glucose is less than 4.7 mmol/L [45]. Our pilot testing showed that use of an individualised blood glucose cut-off (average of fasting blood glucose over two days) rather than 4.7 mmol/L improved adherence to testing and reduced eating when blood glucose was not below the cut-off [78]. Before every desired eating occasion, participants will be instructed to note their intensity of hunger on a 100mm visual analogue scale and their measured blood glucose. If their blood glucose is higher than their personal cut-off, they are advised to engage in some other activity as a distraction and wait at least one hour. At this time, they assess their feelings of hunger again and repeat the measurement if they still want to eat, until their blood glucose is under their individualised cut-off. Over time, participants learn to relate physical feelings of hunger with their blood glucose and to eat only when physically hungry. Participants will be advised to follow this procedure for two weeks. In weeks 3 and 4, the blood glucose testing is optional, but all other recording (intensity and type of hunger, and resulting food intake) continues. Participants will be in regular contact with support staff, who will advise them how to proceed, answer any queries and provide encouragement. In months 2–12, participants will be advised to repeat the recording process (with or without fingerprick blood glucose testing) for one week of every month.

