#### Adherence

Adherence to support strategies will be assessed as follows:

Brief support: attendance at monthly sessions.

App use: frequency, consistency, and comprehensiveness of food recording during first month (daily) and for one week every month for months 2–11 inclusive.

Daily-self weighing: by the number of daily weights recorded in the database.

Hunger training: analysis of the 4-week booklets in month 1 and the weekly recordings for months 2–12 the percentage of times participants measured their glucose before eating, and only ate if blood glucose was lower than the personal cut-off.

Adherence to the dietary regimes will be measured using the 3-day diet records. Those choosing to follow intermittent fasting will complete a 4-day diet record at 6, 12 and 24 months to allow collection of two fasting and two non-fasting days. Adherence to the exercise regime will be measured by the accelerometers. In addition, HIIT participants will wear a Polar RC3 GPS heart rate monitor during all home HIIT sessions for a one-week period at baseline, 3, 6, 9 and 12 months to evaluate intensity attained during the sessions.

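### The hunger-training adherence score counts glucose tests that are optional after week 2, and the app scoring window and the 24-month adherence aim do not match the tasks requested

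*Protocol article*

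**What the plan says.** All places are in the protocol article.

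- **Hunger training, what is asked** (Intervention groups and sessions). Participants measure glucose before each desired eating occasion for two weeks. Then: "In weeks 3 and 4, the blood glucose testing is optional", while the other recording (hunger and food intake) continues. For months 2–12, "participants will be advised to repeat the recording process (with or without fingerprick blood glucose testing) for one week of every month".
- **Hunger training, what is scored** (Adherence). The sources are the four-week booklets and the months 2–12 recordings. The only criterion given is "the percentage of times participants measured their glucose before eating, and only ate if blood glucose was lower than the personal cut-off". No separate rule is stated for the weeks in which testing is optional.
- **App, what is asked** (Intervention groups and sessions). Participants are to "monitor their dietary intake every day for the first month, and for one week of every month for months 2–12".
- **App, what is scored** (Adherence). Daily recording in the first month, then "for one week every month for months 2–11 inclusive".
- **Period of the aim** (Aims and objectives). Secondary aim (ii) is "the degree of adherence to each of the support strategies over the 24 months".
- **Period of the intervention** (Study design). Participants are "randomised to one of the five groups for a 12-month intervention, with further follow-up at 24 months".

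**The concern.** An adherence score should be at its maximum for someone who does what the protocol asks. The hunger-training criterion does not guarantee this. From week 3 a participant may stop testing and still follow every instruction, yet the stated criterion counts only occasions with a glucose measurement. The programme aims to teach people to recognise hunger, so moving on from the meter is something it allows.

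Adherence to each support strategy is a named secondary aim, and adherence is the central rationale of the trial. A low hunger-training figure could be reported as poor adherence when it shows only that optional tests were not done. Comparison with the other strategies, which are scored on things participants were asked to do, would then mislead.

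The other two mismatches are of the same kind: the app is scored over a shorter window than the one prescribed, and the aim names a period twice as long as the app and hunger-training tasks.

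**Working it through.** The plan states no figure for this point, so there is none to reproduce. The check sets the prescribed windows beside the scored windows and counts.

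**Hunger training.** Inputs from Intervention groups and sessions and from Adherence: month 1 is a 4-week programme (28 days), then one recording week (7 days) in each of months 2–12, which is 11 weeks.

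- Recording weeks in the scored material: 4 + 11 = 15. Days: 28 + 11 × 7 = 105.
- Days on which testing is part of the procedure: 2 × 7 = 14, and 14/105 = 13.3%.
- Days on which testing is optional: 14 (weeks 3–4) + 77 (monthly weeks) = 91, and 91/105 = 86.7%.

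Assume equal eating occasions per day, full compliance in weeks 1–2, and let *f* be the share of optional-period occasions that were tested and eaten below the cut-off. The pooled score is (14 + 91*f*)/105:

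- *f* = 0: 14/105 = 13%
- *f* = 0.5: (14 + 45.5)/105 = 57%
- *f* = 1: 105/105 = 100%

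All three participants may have followed every instruction.

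If the same criterion is applied by period, weeks 1–2 give 100% for this participant whatever *f* is, and the later periods give 100*f*%, that is, 0% to 100%. Scoring by period thus protects the first two weeks, but it still leaves the later weeks measuring only the optional step.

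**App.** Monthly weeks requested, months 2–12: 11. Monthly weeks scored, months 2–11: 10. One of 11 is left out. In days, with a 28-day first month: requested 28 + 77 = 105, scored 28 + 70 = 98, and 98/105 = 93%.

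**Period of aim (ii).** The named measures run to month 11 for the app (11/24 = 46% of the stated period) and to month 12 for hunger training (12/24 = 50%). The tasks themselves end at month 12, in line with the 12-month intervention in Study design. For brief support and daily self-weighing, the Adherence section gives no end month. The Abstract gives 24 months for the randomised strategies, and Participants and recruitment also refers to a two-year intervention, so the length of the intervention is itself stated inconsistently.

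**The case against.** The strongest objection is that the hunger-training sentence is being read too firmly. It lacks a connecting word and may name one of several analyses. It may also describe two measures: how often glucose was tested and, where tested, whether eating followed only below the cut-off. It does not say that the 15 weeks are pooled, and an article may leave scoring detail to the full protocol.

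Part of this stands. Pooling is an assumption, and 13% is the bottom of a range. But the other readings do not remove the problem. As two measures, the testing share has the same 13% to 100% range when pooled, and the second share rests only on those who chose to test. If the criterion was meant for weeks 1–2 alone, the text does not say so, and the months 2–12 recordings it names would have no criterion. The criterion is stated, and it does not fit most of the weeks to which it is attached.

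A reader might infer more than the documents support:

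- *That compliant participants will be classed as non-adherent, or that hunger training will look poorly adhered to.* No adherence threshold is set, and the result depends on pooling and on how many optional tests are done.
- *That dropping month 12 flatters the app.* The Background does say that adherence to food and activity monitoring falls over time, but for app use it places the sharp decline after the first month. One of 11 weeks can hardly change a summary, and this may be a slip.
- *That nothing can be said about months 13–24.* There is no app or hunger-training task then to adhere to, so no task data are lost. Table 1 also schedules questionnaires at month 24.
- *That the weight result is affected.* The primary analysis compares the strategies as randomised and uses no adherence variable. The adherence analysis described in the statistical section concerns diet and exercise choices, not support strategies.

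**Conclusion.** The point holds for secondary aim (ii). The stated hunger-training criterion does not match the task on 91 of 105 scored recording days. If pooled, full compliance is compatible with any score from about 13% to 100%, so the score partly reflects an optional step. That range assumes equal eating occasions per week and complete adherence in weeks 1–2; its lower end also assumes no optional testing. Scored by period, weeks 1–2 are sound.

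The app windows contradict each other, with a small effect of 1 of 11 monthly weeks. The 24-month aim conflicts with the 12-month intervention in Study design and with app and hunger-training tasks that end at month 12; those passages must be reconciled. The primary weight analysis is not touched.

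**What to change.** 1. **Hunger training.** Score by period. For weeks 1–2, report the share of eating occasions that were tested and eaten below the personal cut-off. For weeks 3–4 and the monthly recording weeks, report completion of the requested hunger and food-intake records. Describe glucose results in those later weeks only among participants who tested, and give their number.
2. **App.** Reconcile the two windows so that scoring covers the same months as the recording requested.
3. **Aim (ii).** Reconcile the 24-month wording with the intervention length, and limit task adherence to months 1–12, the period in which the app and hunger-training tasks are requested. State the end month for brief support and daily self-weighing too.
4. **Month 24.** If behaviour at month 24 is described, label it as sustained behaviour, not adherence. The questionnaires scheduled in Table 1 can serve: the self-monitoring questionnaire for weighing and tracking, and the Intuitive Eating scale for eating in response to hunger cues. The self-monitoring questionnaire as described does not capture hunger-training behaviour, so it should not stand in for that arm.

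The cost is a change of wording. The booklets, weekly recordings and questionnaires are already planned, so no new data are needed. What is given up is the claim to measure task adherence over the full 24 months.

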Two promising and popular dietary approaches, despite relatively little research around their use in humans, include paleolithic diets and intermittent fasting. Paleolithic diets are based on evolutionary principles and include meat, fruit, vegetables and nuts/seeds while eschewing grains, dairy, and processed foods. Early small studies have provided encouraging results [54–56]. However, whether overweight adults can adhere to paleolithic-type diets in the longer-term requires study. Intermittent fasting is usually defined as normal food intake 3–5 days a week and dramatically reduced intake (down to 2 MJ from typical intake of 8–10 MJ) for 2–4 days. Anecdotally this is believed to be much easier than reducing energy intake by a smaller amount (usually 2 MJ/day) *every* day, which forms part of the current guidelines. While a wealth of animal data supports the effectiveness of intermittent fasting for weight control [57], research in humans is less certain [58]. However, the small amount of data available does show modest evidence of effectiveness for treatment of obesity and cardioprotection [59, 60].

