### Choice of diet and exercise plan

If a participant is eligible and has completed all baseline assessments, they will be provided with information on each of the possible three dietary and two exercise approaches, and allowed to choose which might suit them best.

Their choice of dietary approaches will be:*Mediterranean* – High amounts of fruit, vegetables and wholegrain cereals, moderate amounts of protein (particularly from fish), nuts (up to 30 g per day), olive oil and dairy foods, and limited amounts of processed and sugary foods. Calorie counting will not be required (unless randomised to MyFitnessPal), but energy intake should be reduced by appropriate levels through promotion of appropriate foods and serving sizes.*Modified paleolithic* – Strict paleolithic diets remove all processed and cereal-based foods, legumes and dairy products which we believe is not sustainable for most overweight people long-term. Participants who choose this diet can decide to remove these foods; but we will also suggest they follow an 80:20 rule where up to one serving of dairy products, legumes and appropriate low glycaemic index, wholegrain carbohydrates are allowed each day. We believe this still fits the paleolithic philosophy while promoting greater long-term adherence through flexibility. Calorie counting will not be required (unless randomised to MyFitnessPal), but energy intake should be reduced by appropriate levels through promotion of appropriate foods and serving sizes.*Intermittent fasting (5:2 plan)* – Participants choose two days per week (any days, not consecutive, can vary from week to week to fit lifestyle) where energy intake cannot exceed 2 (females) – 2.5 (males) MJ. In practice, this usually means a small breakfast (e.g. plain porridge), no or limited food during the day, and non-starchy vegetables only for the evening meal, although other variations are possible. Participants can eat *ad libitum* on the remaining days.

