#### Diet, physical activity and fitness

Participants will complete a weighed 3-day diet record (one weekend day, two week days) with energy and nutrient intakes calculated using Kai-culator (University of Otago, 2011). Physical activity (counts per minute and intensity categories) and sleep duration and timing (minutes, bed time, wake time) will be measured using ActiGraph accelerometers (GT3X, ActiGraph, Pensacola, FL) worn around the waist over 7 days. Participants wear the accelerometers for the full 24-hour periods, which provides both sleep and activity data and lowers the chance of missing data from participants not remembering to reattach the accelerometer straight after waking. Aerobic fitness will be evaluated by estimating participants’ VO^2^max, using the YMCA submaximal cycle ergometer test [80].

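### The intermittent fasters' diet record is planned around two fasting and two non-fasting days, so it cannot measure how often they fast, and no listed instrument does

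*Protocol article*

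**What the plan says.** Under Choice of diet and exercise plan, the 5:2 option is defined by a frequency and a limit. The frequency is "Participants choose two days per week (any days, not consecutive, can vary from week to week to fit lifestyle"); the limit applies to those days, "where energy intake cannot exceed 2 (females) – 2.5 (males) MJ". Eating on the other days is unrestricted.

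Under Adherence, the general rule is "Adherence to the dietary regimes will be measured using the 3-day diet records". The exception follows: "Those choosing to follow intermittent fasting will complete a 4-day diet record at 6, 12 and 24 months", and its purpose is "to allow collection of two fasting and two non-fasting days". Under Diet, physical activity and fitness, the standard instrument is described differently: "Participants will complete a weighed 3-day diet record (one weekend day, two week days"). That is also the form of the baseline record, including for people who go on to choose fasting.

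Dietary intake is among the outcomes in secondary aim (i). Secondary aim (iii) covers adherence to the diet and exercise "plans that are selected over the 24 months and the outcomes within these self-selected groups". The statistical section then plans a cohort analysis that compares adherence between diets and relates it to outcomes. The questionnaires described cover eating behaviour, mood, self-monitoring, self-efficacy and satisfaction, among others. None is described as counting fasting days. The article gives no rule for combining recorded days into a mean intake.

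**The concern.** Fasting twice a week is what distinguishes this diet from the other two. Adherence to it has two parts: how often the participant fasts, and whether intake stays within the limit on those days. A record planned to hold two fasting days speaks to the second part. On the first, the count largely reflects the instruction.

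At stake is aim (iii) for one of the three diets, and any cohort result that links adherence in that diet to weight or other outcomes. The gap lies in data collection: if frequency is not asked at the visit, a later analysis plan cannot supply it.

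There is also a question about intake. The record holds fasting days in a different proportion from the week it is meant to represent. If that is ignored in the analysis, fasters' follow-up intake is understated, whereas their baseline record and the other diets' records are unaffected.

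**Working it through.** The article states no figure on this point that could be reproduced, so the check is direct arithmetic.

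**Inputs**
- Prescribed fasting days: 2 of 7 (Choice of diet and exercise plan).
- Fasting-day intake F: 2 MJ (women) or 2.5 MJ (men), the limits in the same section, assumed to be met exactly.
- Other-day intake A: 8 to 10 MJ. This is an assumption. The plan sets no figure for these days; the range is the typical intake in the Background ("dramatically reduced intake (down to 2 MJ from typical intake of 8–10 MJ) for 2–4 days").
- Record: 2 fasting and 2 other days (Adherence).

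**Step 1: share of fasting days.** Record 2/4 = 50 %; week 2/7 = 28.6 %. Ratio 0.50/0.286 = 1.75.

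**Step 2: frequency.** With k fasting days a week, true mean intake is (kF + (7 − k)A)/7. A record that holds two days of each type does not depend on k. With F = 2 and A = 8:

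| k (days/week) | Plain record mean | Record weighted 2/7 and 5/7 | True weekly mean |
|---|---|---|---|
| 1 | 5.00 | 6.29 | 7.14 |
| 2 | 5.00 | 6.29 | 6.29 |
| 3 | 5.00 | 6.29 | 5.43 |

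(MJ/day.) The three participants differ in adherence but return the same record. Weighting by 2/7 and 5/7 is right only in the middle row, because it assumes the frequency that has to be measured. Each fasting day of error in k shifts the weekly mean by (A − F)/7 = (8 − 2)/7 = 0.86 MJ/day.

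**Step 3: intake, if the four days were simply averaged.** The plain mean is (2F + 2A)/4. The weekly mean for a fully adherent faster is (2F + 5A)/7. The difference is −3(A − F)/14.

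| F | A | Plain mean | Weekly mean | Difference | Percent |
|---|---|---|---|---|---|
| 2 | 8 | 5.00 | 6.29 | −1.29 | −20.5 |
| 2 | 10 | 6.00 | 7.71 | −1.71 | −22.2 |
| 2.5 | 8 | 5.25 | 6.43 | −1.18 | −18.3 |
| 2.5 | 10 | 6.25 | 7.86 | −1.61 | −20.5 |

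The range is 1.18 to 1.71 MJ/day, or 18 to 22 %. For scale, the Background gives 2 MJ/day as the usual daily reduction under current guidelines; 1.18/2 = 59 % and 1.71/2 = 86 % of that.

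**The case against.** The strongest reply is that recording both day types is good design. Fasting days move from week to week, so a standard three-day record might catch none, one or two of them. Two of each type gives an estimate for both, which is what a correctly weighted mean needs. How the days are combined is a matter for an analysis plan that is not shown, and its absence from an article is no fault. This stands. The intake bias is therefore conditional, and a reader who infers that reported intake will be understated goes beyond the text.

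Second, the article states the two-plus-two composition as an aim. Nothing says that a record with fewer fasting days is rejected, so someone who has given up fasting could return none. This also stands, but it reveals abandonment rather than partial adherence. A record with one fasting day could come from a person who fasts weekly, or from one who fasts twice but did not record the second day.

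Third, the questionnaires are described in summary, so an unlisted item on fasting cannot be excluded. If one exists, the frequency gap closes; the article does not mention it.

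Three stronger readings are tempting and are not supported:
- *That the artefact biases the comparison of support strategies because diet is not a stratification factor.* Diet is chosen before randomisation, so the share of fasters is balanced between arms in expectation. Chance imbalance would add noise, and the article says that an analysis adjusting for diet will be considered.
- *That a person who fasts once a fortnight would supply a perfect record.* The baseline record is completed within a week, but the follow-up recording window is not stated. In a one-week window such a person would have at most one fasting day to record, unless behaviour changed for the recording.
- *That adherence would be overstated relative to the Mediterranean and Paleo groups.* No adherence score is given for any diet, so the direction of a between-diet difference cannot be derived.

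**Conclusion.** The point holds in a limited form. Diet records are the only stated measure of dietary adherence, and the fasters' record is planned in a way that cannot measure weekly fasting frequency. That weakens aim (iii) and the cohort analysis for this self-selected group. This part needs no numerical assumption; it rests on the recording rule and on no other listed instrument counting fasting days.

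The intake part is conditional on an unweighted mean, full adherence, and the assumed 8 to 10 MJ on other days. On those terms the understatement of 1.2 to 1.7 MJ/day would distort change from the three-day baseline record and comparisons between diets. A fixed 2/7 and 5/7 weighting would remove it only for participants who do fast twice a week.

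The severity is minor: secondary outcomes in one diet group.

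**What to change.** Add one item for fasters to the existing 6-, 12- and 24-month questionnaires: the number of fasting days in each of the last four weeks. Then:
- Let k be the mean weekly count and use it as the measure of adherence to fasting frequency.
- Use the diet record only for adherence to the fasting-day energy limit.
- Compute fasters' mean intake at follow-up as (k × fasting-day mean + (7 − k) × non-fasting-day mean)/7. At k = 0 the fasting term drops out.

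The cost is one question for one subgroup at visits that already take place, and one weighting step in the analysis. Treatment, visits and the diet record stay as they are. The drawback is that k is self-reported and subject to recall and social desirability. The item has to be in place before the follow-up visits, since past frequency cannot be reliably reconstructed later.
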